**Fig 3 pone.0326482.g003:**
[figure not shown]
Image of Pneumowave chest sensor and location of placement on the body.

Participants are asked to wear the biosensor as consistently as possible during their stay in the hostel. They are not required to wear it outside the facility. Hostel staff assist with basic maintenance, including support for battery replacement and electrode changes. Staff and participants are provided with brief training and written guidance.

Upon enrolment, participants will receive a wearable biosensor that monitors chest motion and transmits data to a Hub. The study procedures include:

Demographics and baseline assessment: collection of age, gender, health status (including respiratory conditions) and opioid use history (abbreviated AIR tool [15,16].Biosensor data: duration worn, number of useable hours recorded, signal qualityDrug use diary: participants will self-report drug use via a confidential diary.Overdose reporting: any overdose events observed or reported are documented by hostel staff using a structured formSatisfaction surveys: A brief questionnaire administered to participants to capture perceptions of comfort, usability, and willingness to use the device long term. At least one survey will be completed by each participant to assess usability and comfort, at 4 weeks.Qualitative interviews and focus groups: will be conducted with participants and staff to explore experiences, perceived benefits, and challenges of using the technology.

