#### Rationale for study procedures.

Several key decisions were made in designing this study to maximise feasibility and data quality:

Drug diaries: Self-reported drug use diaries were chosen as they allow for frequent participant input, utilised for matching self-reported substance use recorded chest motion data. This method was also successfully utilised in RESCU-1, making it a logical approach for RESCU-2 to maintain consistency.Study setting selection: Supported accommodation settings were chosen due to their role in supporting individuals who might be at risk of overdose. This setting allows for real-world assessment and evaluation of biosensor use, which is essential for its future potential in these settings to prevent fatalities.Use of a Hub for data transmission: Instead of relying on participants’ personal devices or providing a smartphone or tablet, the study employs a dedicated Hub to collect and transmit biosensor data. This decision was made in collaboration with accommodation staff for a number of reasons: to reduce technological barriers, ensure reliable data capture across different sites, reduce vulnerability to theft, or risk that the devices could be sold.Participant and Patient Involvement (PPI) and a senior qualitative researcher (PR) informed the topic guide of the study

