### Biosensor analyses

#### Reference event.

Evidence of reduced and no chest movement within the sensor data will be compared to the observed and recorded reference events. Reference events will comprise of staff observed events and reports and drug use diary records. Staff-identified events are any event that has required an intervention by staff in the hostel. Interventions can range from a simple audio stimulus, up to and including requesting an ambulance to attend. These events include those where overdose may not have occurred, but the response will have been managed in the same way according to the site’s incident response. These incidences will be recorded as an ‘acute event’ or ‘prompt event’. Where an overdose has been clearly identified using the tools mentioned above, these incidences will be identified as ‘overdose event.’ Analysis will incorporate both types of ‘reference’ events. Biosensor data will be analysed over a period of 30 minutes prior to each reference event. We expect the following possible scenarios to occur: 1) no opioid use reported, overdose event; 2) opioid use reported but no overdose event; 3) opioid use and overdose event.

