### Strengths and weaknesses

A major strength of this study is its focus on real-world implementation of the PneumoWave DC system in a setting where overdose risk is high, but immediate medical supervision is not always available. The inclusion of both quantitative and qualitative data enhances the comprehensiveness of the findings, allowing for a deeper understanding of both technical feasibility and useability. By capturing structured metrics and nuanced user feedback, the study will generate findings that are directly relevant to service providers, researchers and policymakers.

Limitations include the reliance on self-reported drug use data, which may be influenced by recall bias or social desirability effects. Drug use diaries, essential for accurately correlating chest motion data with drug administration, may be incomplete or lack sufficient detail. While qualitative insights offer valuable context, subjective responses may not always align with objective biosensor data. Additionally, practical and technical factors, such as device connectivity disruptions and data transmission variability may affect the completeness of the database.

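### The 30-minute look-back window also covers diary records of drug use, where it reads breathing before the drug rather than after it

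*Protocol article*

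**What the plan says.** The rule is in the Reference event section, under Biosensor analyses. The section first defines the reference: "Reference events will comprise of staff observed events and reports and drug use diary records". It distinguishes staff-identified acute or prompt events from clearly identified overdose events and adds "Analysis will incorporate both types of ‘reference’ events". It then fixes the window: "Biosensor data will be analysed over a period of 30 minutes prior to each reference event". No exemption is written for diary records, and no window after an event is given. Three scenarios follow. The second is "opioid use reported but no overdose event" and the third is "opioid use and overdose event".

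The purpose of the diaries is stated twice. Rationale for study procedures says they are "utilised for matching self-reported substance use recorded chest motion data". Strengths and weaknesses calls them "essential for accurately correlating chest motion data with drug administration". On how entries are made, the list under Study procedures says only that "participants will self-report drug use via a confidential diary". It does not say whether an entry carries the time of use or the time of writing.

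**The concern.** A drug can change breathing only after it is taken. A window that closes at the moment of use therefore holds the participant's pre-drug breathing and none of the response. The rule defeats the diaries' stated purpose for any record timed at use.

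Records of use without overdose are the most exposed, because a diary entry may be their only time anchor. They are also an informative comparator, since they show opioid exposure that did not lead to overdose. Reading them before use would put unexposed breathing in the comparator's place.

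There is a second consequence in the Algorithm under test section and the secondary outcomes, where detections are compared with reference events and classified as true positive, false positive or false negative. The look-back is the only window the article gives for linking the sensor to a reference event. If it also governs matching, reduced movement detected shortly after reported use falls outside it. That detection could be scored as unmatched, and the diary record would appear to have no signal.

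**Working it through.** No sample size, power or error rate is involved, and the 30 minutes is a design rule with no derivation to reproduce. The check is interval arithmetic.

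**Inputs from the article.** The window is 30 minutes, backward only, and applies to each reference event. Diary records are reference events. The time attached to a diary record is not stated.

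**Assumed inputs.** The lags between use and the reference time (5, 15, 30 and 60 minutes) are illustrative, because the article gives none.

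**Formula.** Let U be the time of drug use, T the time of the reference event and L = T − U. The window is [T − 30, T]. For L ≥ 0 it runs from L − 30 to L minutes relative to use, and the post-use minutes inside it are min(30, max(0, L)).

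| Lag L (min) | Window relative to use (min) | Post-use minutes of 30 |
|---|---|---|
| 0 (record timed at use) | −30 to 0 | min(30, 0) = 0 |
| 5 | −25 to +5 | min(30, 5) = 5 |
| 15 | −15 to +15 | min(30, 15) = 15 |
| 30 | 0 to +30 | min(30, 30) = 30 |
| 60 | +30 to +60 | min(30, 60) = 30 |

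**Reading the table for diary records.** With L = 0 the whole window lies before the drug. With entry-timed records the mix of pre-use and post-use breathing differs from record to record, driven by when the participant wrote the entry. At L = 60 all 30 minutes are post-use, but the first 60 − 30 = 30 minutes after use are missed.

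**Matching example.** Suppose reduced movement occurs 10 minutes after use (an assumed time). It is outside the window at L = 0 and L = 5, inside at L = 15 and L = 30, and outside again at L = 60. The same breathing event would be matched or unmatched according to diary habit alone.

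**Reading the table for staff events.** The same arithmetic works in the rule's favour when T is a staff-identified event some time after use. With L of 5, 15 or 30 minutes the window holds 5, 15 or 30 post-use minutes. When use and overdose both occur, the staff event can therefore supply post-use data.

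**The case against.** **Other analyses are not tied to the window.** A reader might infer that the drug effect is never analysed. The article does not support that. The Algorithm under test section has the stored data processed for reduced chest movement without restricting it to 30-minute windows. The secondary outcomes count events of reduced or absent movement and compare traces from suspected overdose and non-overdose periods, again without naming the window. A staff event after use can also bring post-use minutes into its own look-back. This objection stands and limits the point to how diary records are linked to the trace.

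**The rule may be meant for staff events only.** The two types of reference event could be acute or prompt events and overdose events, with the diary serving only to classify them. The use-without-overdose scenario could then be a staff prompt event with reported use. This reading is plausible and makes the intended scope less certain. It does not remove the wording, which lists diary records as reference events and applies the window to each one.

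**Entirely pre-drug content is not certain.** This is correct. It holds only if records are timed at use. Timing at entry does not rescue the rule, because the content then varies with an unknown lag.

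**The article is condensed, and the registered analysis plan is not shown.** A missing detail could be left to that plan. Here the article states a rule, and the rule as stated gives the wrong window for one class of event.

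**Staff events.** A reader might infer that the look-back also fails for staff events by missing the onset or the response. The article gives no discovery delays from which to show this. An event that has already developed at discovery lies in the preceding minutes. Running the window through the response would mix in stimulated or treated breathing, which is a trade-off and does not correct an error. No fault is found there.

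**Conclusion.** Wrong as written, with moderate severity. Applied literally, the rule gives 0 of 30 post-use minutes for a diary record timed at use, and an uncontrolled mix for one timed at entry, contrary to the purpose the article gives the diaries.

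The conclusion rests on reading each reference event as including diary records, which the text says. The figure of zero also needs the record to be timed at use, which the text does not say. The effect on matching further assumes that the look-back defines a match.

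Severity is limited because event detection is a secondary outcome and algorithm performance is assessed only if possible and may be exploratory. No primary outcome on feasibility, acceptability or technical capture uses this window.

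**What to change.** Replace the single rule with two.

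- **Staff-identified events:** keep the 30-minute look-back.
- **Diary-reported opioid use:** anchor on the reported time of use and analyse a forward window whose length is fixed before analysis. Use the 30 minutes before use as the participant's own baseline. Add a sensitivity analysis that widens the window to allow for error in the diary time.

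State in the same paragraph whether a diary record is timed at use or at entry, and say that the event-specific window is the one used to match detections to reference events. If the registered analysis plan already does this, align the article with it.

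The cost is one paragraph of wording and slightly more trace processing. No new data are needed, because the sensor data are transmitted continuously. If some diary entries carry only a time of writing, the widened window is where that uncertainty is handled. Status and timeline reports that no results had been generated at the time of writing, so on that account the rule could be corrected ahead of the analysis.

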#### Algorithm under test.

The PneumoWave Hub transmits Biosensor data to a Cloud Storage facility. The stored data is then processed using experimental algorithms for the presence of reduced chest movement events.

The performance of the Algorithm (Under Test, AUT) will be compared to the reference events at the hostels in terms of the AUT’s sensitivity and false alarm rate, if this is possible. If the target numbers for sample size and acute events are not reached, analysis will still be possible and feasible, but it may be exploratory.

#### Qualitative analyses.

Focus group and interview audio recordings will be transcribed verbatim. Transcripts will be analysed and a coding framework will be developed using thematic analysis, specifically an inductive thematic approach (Braun & Clarke, 2006). Thematic analysis will help identify explicit meanings arising from the interviews and enable the interpretation of underlying, implicit meanings. This approach will provide insights into participants’ attitudes, feelings, and perceptions regarding the acceptability of wearing the device, and support the identification of suitable strategies for developing a clinical intervention pathway.

Multiple researchers will review transcripts to ensure coding reliability and identify recurring themes related to:

Participant experiences of wearing the biosensorPerceived barriers and facilitatorsAcceptability in day-to-day useStaff perspectives on device integration into overdose response workflows

NVivo or equivalent software will be used to support coding and data organisation. Emerging themes will be compared across stakeholder groups (residents vs staff) to explore shared and divergent perspectives. Qualitative findings will be integrated with quantitative results to provide a comprehensive assessment of feasibility and acceptability.

### Protocol amendments and early termination

Any significant amendments to the study protocol will be reviewed and approved by the REC and the study sponsor. Participants who lose capacity will be withdrawn from the study to ensure ethical compliance. The study may be terminated early due to safety concerns, funding constraints, or administrative decisions, with appropriate reporting to regulatory bodies.

### Status and timeline

This study is part of a 12-month funded study. Funding started in September 2024, when approvals were sought and sites were set up from September to December 2024. The first participant was recruited on 28 January 2025 and is ongoing. Recruitment and data collection will continue until 31 July 2025. Data analysis and results have not yet been generated. Data analysis and results are expected in August 2025 with the final report expect to be completed by 31 August 2025, with dissemination following thereafter.

Although the original protocol included the possibility of enrolling short-term or overnight residents, and this is described in the manuscript, early consultation with participating services indicated that identifying and engaging this group in a meaningful way would not be feasible. As a result, recruitment has focused exclusively on longer-term residents, who are more stable and accessible for follow-up and data collection.

## Discussion

Opioid overdose continues to be a leading cause of drug-related mortality worldwide, with increasing concerns about its impact on vulnerable populations. Traditional harm reduction strategies, including supervised consumption facilities and naloxone distribution, are effective for some but remain limited in their reach and accessibility. Wearable biosensors represent an emerging technological solution to this crisis, offering real-time physiological monitoring that may facilitate early intervention and overdose prevention. This study examines the feasibility and acceptability of the PneumoWave biosensor to monitor chest motion in supported accommodation settings, contributing to the growing body of research exploring digital health interventions for substance use disorders.

### Limitations of study design

As an observational study without a control group, this research does not allow for causal inferences regarding the effectiveness of the PneumoWave DC system in preventing overdose-related fatalities. Additionally, participant adherence may vary, potentially affecting data consistency. The study is conducted within supported accommodation facilities, which will not fully represent the broader community of individuals at risk of opioid overdose. Variability in participant engagement and technical challenges related to biosensor use may also introduce potential biases.

### Comparison with similar work

Previous studies, such as those conducted in medically supervised injecting centres [17], have assessed the feasibility of wearable biosensors for opioid overdose detection. The ODSEEN study, for example, has examined the PneumoWave system in a supervised drug consumption setting, yielding promising results regarding its ability to utilise recorded chest motion to develop an application to detect respiratory depression. Another study monitored people who had used opioids in a women’s shelter in the USA using continuous pulse oximetry [18].

However, the current study expands upon previous work by evaluating the device in supported accommodation settings where supervision is less structured, reflecting real-world usage conditions more accurately. Unlike prior research focusing on short-term biosensor use during single drug consumption events, RESCU-2 explores long-term feasibility, adherence, and acceptability among individuals in semi-independent living environments.

Findings from this study will be compared with previous research on wearable biosensors for opioid overdose prevention, including RESCU-1 which is currently in preparation and evaluates the same chest sensor, in an earlier prototype form, among participants who wear it at home while receiving OST. Additionally, comparisons will be drawn with broader studies examining the feasibility and acceptability of wearable devices designed to address the overdose crisis [12,19–23]. The effectiveness and user acceptability of these technologies have shown considerable variation, reflecting differences in study populations, device designs, and monitoring settings. While there is a growing body of research in this field, most studies focus on technologies that are still in early development or have yet to be widely implemented in real-world harm reduction settings [24]. Currently, there is no published work evaluating a remote chest sensor capable of reliably detecting chest wall movement in the context of opioid overdose, highlighting the unique contribution of this study to the existing literature.

### Strengths and weaknesses

A major strength of this study is its focus on real-world implementation of the PneumoWave DC system in a setting where overdose risk is high, but immediate medical supervision is not always available. The inclusion of both quantitative and qualitative data enhances the comprehensiveness of the findings, allowing for a deeper understanding of both technical feasibility and useability. By capturing structured metrics and nuanced user feedback, the study will generate findings that are directly relevant to service providers, researchers and policymakers.

Limitations include the reliance on self-reported drug use data, which may be influenced by recall bias or social desirability effects. Drug use diaries, essential for accurately correlating chest motion data with drug administration, may be incomplete or lack sufficient detail. While qualitative insights offer valuable context, subjective responses may not always align with objective biosensor data. Additionally, practical and technical factors, such as device connectivity disruptions and data transmission variability may affect the completeness of the database.

### Dissemination plans

Findings from this study will be disseminated through peer-reviewed journal publications, conference presentations, and community reports tailored for stakeholders. Participants who remain in supported accommodation at the time of publication will receive a summary of results. Insights will also be shared with policymakers to inform future initiatives and potential integration of biosensor technology into public health strategies.

## Conclusion

The RESCU-2 study aims to provide crucial insights into the feasibility and acceptability of wearable biosensors for overdose detection in supported accommodation settings. By assessing both technical performance and insights on facilitators and barriers on use of the technology, this research will help determine the potential for integrating real-time respiratory monitoring into relevant settings. Findings from this study will inform future interventions and policy decisions aimed at reducing opioid-related mortality in high-risk populations.
